## Abstract

**Background:**

Continuous monitoring of patients’ vital signs is critical for early detection of postoperative complications. Traditional manual monitoring by nursing staff is time-consuming and provides only intermittent data. Wearable devices offer continuous monitoring capabilities, potentially enhancing early warning systems, reducing nurse workload, and facilitating earlier patient discharge. However, research on their implementation and effectiveness in clinical settings remains limited.

**Objective:**

This study aims to evaluate the implementation and feasibility of continuous monitoring using photoplethysmography sensor technology (a viQtor device) in a surgical ward. We will also assess the impact on nursing workload and the usability of this workflow.

**Methods:**

The REQUEST (Remote Monitoring by viQtor Upon Implementation on a Surgical Department) study is a prospective observational implementation study conducted over 8 months in a surgical ward. The vital signs of 500 postoperative patients will be continuously monitored using the viQtor device, which measures heart rate, respiratory rate, and oxygen saturation. The study consists of 2 phases: an initial period with manual spot checks, followed by a phase using the wearable device as the primary monitoring tool. Outcomes include the Integrated Workload Scale for nursing workload and a framework evaluating acceptability, feasibility, adoption, and sustainability. Data collection involves device performance metrics, questionnaires (the Evidence-Based Practice Attitude Scale and the System Usability Scale), and thematic analysis of focus groups.

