## Methods

### Setting

This prospective implementation study with retrospective data analysis (the REQUEST [Remote Monitoring by viQtor Upon Implementation on a Surgical Department] trial) will be conducted at a large teaching hospital. All adult patients (aged 18 years and older) admitted to the surgical department for elective procedures will be eligible for inclusion, provided they meet our inclusion criteria and provide informed consent. Patients unable to wear the device or unwilling to participate will be excluded.

The viQtor device, developed by SMARTCARE, was selected due to its proven capability for autonomous, continuous monitoring and its established structure for seamless data transfer into the electronic health record (EHR). The device is CE (Conformité Européenne)-certified and transmits data every minute via a cellular network without the need for any hub. Each vital sign—heart rate, respiratory rate, and peripheral oxygen saturation (SpO₂)—is updated every minute, with data being transferred to the EHR. The device provides median values from the last 4 hours for each vital sign, which means that the system aggregates data over that period to ensure stability in measurements. In the event of missing data, the system generates flags to indicate the absence of readings, and data imputation strategies will be applied. By using clinical-grade photoplethysmography sensor technology, the device allows accurate tracking of heart rate, respiratory rate, and SpO₂. Although the device can also measure skin temperature, this parameter will not be used in this study.
The solution comprises a device with a charger and an armband. The device is worn on the upper arm under clothing and is applied upon admission (Figure 1).

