### Implementation Phase

Implementation of the device as the new standard of care for monitoring will be executed in 2 distinct phases to ensure a thorough evaluation and implementation of this monitoring system (Table 1).

During phase 1 (the initial phase; months 1-3), patients will continue to receive the current standard of care, which involves manual spot checks and MEWS measurements by nursing staff. Concurrently, all health care staff will receive training on the application, data interpretation, and protocol adherence concerning the solution to optimize the infrastructure before its implementation.

Following phase 1 (in month 4; the evaluation and validation period), the preimplementation phase will be evaluated. Predictive accuracy will be evaluated by comparing device data against clinical outcomes such as complications, intensive care unit transfers, or MEWS-triggered interventions using area under the receiver operating characteristic curve analysis.

In phase 2 (months 5-8), the wearable will become the primary tool for patient monitoring, supplemented by manual spot checks by nurses as needed. This phase aims to evaluate the integration into standard care.

During the whole study, every minute data are securely stored. During phase 2 of the study, 6 times a day, median values of the previous 4-hour window will be uploaded to the EHR. In case of signal loss or low-quality readings, the system generates flags, allowing for assessment of signal-to-noise ratio (SNR).

**Table 1 table1:** Psychometric properties and statistical analysis.

Objective	Instrument	Variable	Statistical test	Achievement criteria
Fidelity	SUS^a^	Continuous	Unpaired *t* test or Mann-Whitney *U* test	Fidelity achieved when protocol adherence is ≥95%
Acceptance	SC^b^/day	Continuous	Descriptive statistics	Acceptance achieved when ≥75% of nurses use the device regularly
Acceptance	SC/patient	Continuous	Descriptive statistics	Acceptance achieved when ≥75% of nurses use the device regularly
Acceptance	IWS^c^	Ordinal	1-way ANOVA	Acceptance achieved when ≥75% of nurses use the device regularly
Adoption	EBPAS^d^	Continuous	Repeated measures ANOVA	Adoption achieved when device use exceeds 70% by clinical staff
Appropriateness	SNR^e^	Continuous	Descriptive statistics	Adoption achieved when device use exceeds 70% by clinical staff
Appropriateness	ADE^f^	Continuous	Descriptive statistics	Appropriateness achieved with minimal ADEs

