Feasibility	Thematic analysis	Nominal	Braun and Clarke [11] thematic analysis	Feasibility achieved when 80% of clinicians can successfully implement the device
Time efficiency	Time measurement	Continuous	Descriptive statistics	Time efficiency achieved when nurses’ time spent on monitoring decreases by ≥20%
Predictive accuracy	MEWS^g^ and CREWS^h^	Nominal	AUROC^i^	Predictive accuracy achieved when AUROC ≥0.80

^a^SUS: System Usability Scale.

^b^SC: spot check.

^c^IWS: Integrated Workload Scale.

^d^EBPAS: Evidence Based Practice Attitude Scale.

^e^SNR: signal-to-noise ratio.

^f^ADE: adverse device event.

^g^MEWS: Modified Early Warning Score.

^h^CREWS: Continuous Remote Early Warning Score.

^i^AUROC: area under the receiver operating characteristic curve.

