Approximately 70 nurses from the surgical ward will participate in the study and complete the IWS. In addition, 10 nurses and 5 physicians will voluntarily join focus groups to conduct an in-depth evaluation of the new implementation. These focus groups, which will be established prior to the study’s commencement, will meet 3 times during the study period to discuss the progress of the study and share their experiences with the implementation. A structured analysis of fidelity, feasibility, and acceptability will be conducted by the focus group, and this information will be processed and objectified using a thematic analysis devised by Braun and Clarke [11].

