## Results

Staff training was completed in October 2024, and full implementation is ongoing. Up to 150 participants intend to be enrolled in the study. Preliminary findings, including data on usability and workload, are expected by July 2025 (see details in Table 2).

**Table 2 table2:** Measurement timetable for psychometric properties.

Objective	Instrument	0^a^	1	2	3	4 (evaluation/validation)	5	6	7	8 (evaluation/validation)
Fidelity	SUS^b^						Q^c^			Q
Acceptance	SC^d^/day				AD^e^					AD
Acceptance	SC/patient				AD					AD
Acceptance	IWS^f^	Q			Q		Q	Q	Q	Q
Adoption	EBPAS^g^	Q			Q				Q	Q
Appropriateness	SNR^h^									AD
Appropriateness	ADE^i^									AD
Feasibility	Thematic analysis				FG^j^			FG		FG
Time efficiency	Time measurement		M^k^	M	M		M	M	M	M
Predictive accuracy	MEWS^l^ and CREWS^m^		M	M	M	AD and M	AD (and M)	AD (and M)	AD	AD

^a^Numbers 0-8 represent the study months, starting from baseline (month 0) through to month 8.

^b^SUS: System Usability Scale.

^c^Q: questionnaire.

^d^SC: spot check.

^e^AD: administered data.

^f^IWS: Integrated Workload Scale.

^g^EBPAS: Evidence Based Practice Attitude Scale.

^h^SNR: signal-to-noise ratio.

^i^ADE: adverse device event.

^j^FG: focus group.

^k^M: manual measurement.

^l^MEWS: Modified Early Warning Score.

^m^CREWS: Continuous Remote Early Warning Score.

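### The Abstract plans 500 monitored patients but the Results cap enrolment at 150 participants; both cannot hold, and patient-level precision differs about 1.8-fold between them

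*Protocol article*

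**What the plan says.** The Methods paragraph of the Abstract gives a count of patients: "The vital signs of 500 postoperative patients will be continuously monitored using the viQtor device". The Results section gives a ceiling on a less specific group: "Up to 150 participants intend to be enrolled in the study".

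The body of the Methods gives no patient number that could decide between them. Setting defines who may enter: "All adult patients (aged 18 years and older) admitted to the surgical department for elective procedures will be eligible for inclusion", subject to the inclusion criteria and informed consent. Ethical Considerations requires written consent from every participant before inclusion. Outcomes gives the staff numbers separately: "Approximately 70 nurses from the surgical ward will participate in the study and complete the IWS", and "10 nurses and 5 physicians will voluntarily join focus groups".

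Table 1 fixes one criterion whose precision depends on the number of patients: "Predictive accuracy achieved when AUROC ≥0.80".

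**The concern.** The article states its planned size twice and the figures differ by a factor of 3.3. A reader cannot tell which is the target. If recruitment stopped at 150 patients, the study would look complete against the Results section and 70% short against the Abstract.

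The patient-level results are the ones directly at stake: the AUROC judged against 0.80, the signal-quality summaries and the count of adverse device events. Predictive accuracy is declared achieved on an observed value, so the number of patients behind that value determines how far a pass or a fail can be trusted.

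**Working it through.** **1. Can either figure be reproduced?** No. The article gives no error rate, power, effect size, standard deviation or event rate from which 500 or 150 would follow. That is not counted as a fault, because an article may leave the calculation to the full protocol. The check is whether the two stated totals can both be true.

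**2. Possible reconciliations.**
- *Participants means patients only.* 500 / 150 = 3.33, so the Abstract exceeds the ceiling more than threefold.
- *Participants means staff only.* Staff come to 70 + 5 = 75 if the focus-group nurses are among the 70, or 70 + 10 + 5 = 85 if they are additional. Neither is 150.
- *Participants means patients and staff.* Then 150 − 75 = 75 or 150 − 85 = 65 patients remain, which is further from 500.
- *One figure refers to a phase or a subset.* The article does not say so anywhere.

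**3. Effect on precision in general.** Interval width scales with 1/√n, so the ratio is √(500/150) = √3.33 = 1.83. For a proportion p, the 95% half-width is 1.96 × √(p(1 − p)/n):
- p = 50%: 4.4 percentage points with 500, 8.0 with 150.
- p = 10%: 2.6 percentage points with 500, 4.8 with 150.

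**4. Effect on the AUROC.** The Hanley-McNeil standard error for AUROC A, with e patients who have the event and m who do not, is

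SE² = [A(1 − A) + (e − 1)(a − A²) + (m − 1)(b − A²)] / (e × m), where a = A/(2 − A) and b = 2A²/(1 + A).

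At A = 0.80, a = 0.6667, b = 0.7111 and A² = 0.64, so a − A² = 0.0267 and b − A² = 0.0711.

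Worked at an assumed 20% event rate:
- n = 500 (e = 100, m = 400): (0.16 + 2.64 + 28.37)/40,000 = 0.000779; SE = 0.028; half-width 1.96 × SE = 0.055.
- n = 150 (e = 30, m = 120): (0.16 + 0.77 + 8.46)/3,600 = 0.00261; SE = 0.051; half-width = 0.100.

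The article gives no event rate, so the range is shown, assuming that every patient enters the analysis. The last column is the case in which 150 includes 75 staff.

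| Assumed event rate | 500 patients | 150 patients | 75 patients |
|---|---|---|---|
| 5% | 0.106 | 0.193 | 0.274 |
| 10% | 0.076 | 0.138 | 0.196 |
| 20% | 0.055 | 0.100 | 0.142 |
| 30% | 0.046 | 0.084 | 0.120 |

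The ratio of the 150 column to the 500 column is about 1.8 in every row. At 5% the smaller samples contain very few events (7.5 and 3.75 on average). The 0.274 entry would carry the upper limit past 1, so it should be read only as a sign that the estimate would be uninformative.

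**The case against.** The two sentences do not count the same thing. The Abstract counts patients monitored, and the Results count participants enrolled. Since the device is to become standard monitoring in phase 2, one could suppose that 500 patients wear it and only 150 are enrolled as study participants. The article never says this, and its consent requirements in Setting and Ethical Considerations weigh against it. What stands is that *participants* is ambiguous, since nurses are also said to participate, and the repair has to define the word.

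A reader might infer that the primary outcome is compromised as well. The documents do not support that. The Integrated Workload Scale is completed by about 70 nurses, and that number is the same whichever patient total is right. Patient numbers bear on it only indirectly, through how often nurses work with the device. That exposure cannot be calculated from the article, which gives neither length of stay nor ward size.

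A reader might also infer that patient-level precision is wholly undefined. If both figures count patients, precision is bracketed by the two. If 150 includes staff, it is worse than the lower figure implies.

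The AUROC half-widths depend on assumed event rates and on all patients being analysed. Implementation Phase places this evaluation in month 4, after phase 1, while Table 2 lists the underlying data through month 8. The number actually analysed could therefore be smaller than either total. This objection stands, and it is why the figures are given as a conditional range.

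**Conclusion.** The inconsistency is real: at least one of the two stated totals is wrong or mislabelled, and nothing in the article reconciles them. They differ 3.3-fold in number and about 1.8-fold in the width of patient-level intervals; that second ratio does not depend on the event rate. The absolute AUROC half-widths, 0.106 to 0.046 with 500 patients and 0.193 to 0.084 with 150, rest on assumed event rates of 5% to 30%, an AUROC of 0.80 and inclusion of every patient.

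It is tempting to conclude that 150 is the true patient number and that the Abstract overstates the study. The article does not establish this. Writing 150 patients into the Abstract would introduce a new error if that figure includes staff.

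**What to change.** 1. Establish the planned number of patients and state it identically in the Abstract and the Results.
2. Say in the Results whether *participants* means patients only. The staff numbers already stand in Outcomes and need no change.
3. If the patient number is below 500, correct the Abstract and report the AUROC with its 95% confidence interval alongside the 0.80 criterion, so that readers can see how firmly the criterion is met or missed.

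The cost is wording, plus one interval in the report. No additional patients or change in conduct are needed. The stated size may look less favourable if the lower figure proves to be the right one.

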**Results:**

Staff training was completed in October 2024, and full implementation is ongoing. Preliminary findings, including data on usability and workload, are expected by July 2025.

**Conclusions:**

This study will provide insight into the practical implementation of continuous vital sign monitoring in surgical care. The findings may support future adoption of wearable technology in clinical workflows.

**Trial Registration:**

ClinicalTrials.gov NCT06574867; https://clinicaltrials.gov/study/NCT06574867

**International Registered Report Identifier (IRRID):**

DERR1-10.2196/70707

## Introduction

The health care sector is currently undergoing a significant transformation, with increasing emphasis on integrating smart technologies to enhance patient safety and clinical efficiency. A central innovation in this shift is the use of wearable monitoring devices in hospitals, particularly for patients recovering from major abdominal surgery. These procedures are associated with a high risk of serious adverse events, which could lead to preventable harm if early signs of clinical deterioration—often evident in vital sign changes—go unnoticed [1].

Current early warning systems are based on intermittent manual assessments of vital signs, and the Early Warning Score (EWS), typically performed three times daily. However, research indicates that deterioration in vital parameters often precedes clinical events by several hours. One study found that in approximately 60% of patients who experienced postoperative complications, changes in vital signs had already occurred but were not recognized in time due to the limited frequency of monitoring [2].

Efforts have been made to improve the EWS, such as the development of the Modified Early Warning Score (MEWS), which incorporates oxygen saturation [3,4]. While these adaptations have increased the sophistication of monitoring, the overall predictive value of these systems remains limited [2,5]. Moreover, variation in EWS methodologies and inconsistent validation have raised concerns about reliability in daily clinical practice [6].

Advancements in wearable technology offer a promising alternative. These devices provide real-time, continuous monitoring of vital signs, enabling earlier detection of clinical deterioration and potentially more timely intervention [4,7-9]. In addition, continuous monitoring may reduce the burden of manual assessments on nursing staff. Despite the potential benefits, widespread implementation of wearables in clinical settings remains uncommon. Most studies to date have focused on technical performance, while few have explored how such devices are adopted and integrated into routine care.

Successfully introducing wearable monitoring systems requires attention not only to the technology itself but also to the clinical environment, the needs and attitudes of health care professionals, and the sustainability of new workflows. This study therefore follows the revised Medical Research Council framework for evaluating complex interventions [10], which emphasizes the role of context, stakeholder engagement, and real-world feasibility.

The objective of this study is to evaluate the implementation and feasibility of continuous vital sign monitoring using the viQtor wearable device in a surgical ward. In doing so, the study aims to assess the device’s usability, its impact on nursing workload, and how effectively it can be embedded in standard clinical practice.

## Methods

### Setting

This prospective implementation study with retrospective data analysis (the REQUEST [Remote Monitoring by viQtor Upon Implementation on a Surgical Department] trial) will be conducted at a large teaching hospital. All adult patients (aged 18 years and older) admitted to the surgical department for elective procedures will be eligible for inclusion, provided they meet our inclusion criteria and provide informed consent. Patients unable to wear the device or unwilling to participate will be excluded.

The viQtor device, developed by SMARTCARE, was selected due to its proven capability for autonomous, continuous monitoring and its established structure for seamless data transfer into the electronic health record (EHR). The device is CE (Conformité Européenne)-certified and transmits data every minute via a cellular network without the need for any hub. Each vital sign—heart rate, respiratory rate, and peripheral oxygen saturation (SpO₂)—is updated every minute, with data being transferred to the EHR. The device provides median values from the last 4 hours for each vital sign, which means that the system aggregates data over that period to ensure stability in measurements. In the event of missing data, the system generates flags to indicate the absence of readings, and data imputation strategies will be applied. By using clinical-grade photoplethysmography sensor technology, the device allows accurate tracking of heart rate, respiratory rate, and SpO₂. Although the device can also measure skin temperature, this parameter will not be used in this study.
The solution comprises a device with a charger and an armband. The device is worn on the upper arm under clothing and is applied upon admission (Figure 1).

**Figure 1 figure1:**
[figure not shown]
The viQtor device placed on the upper arm.

### Implementation Phase

Implementation of the device as the new standard of care for monitoring will be executed in 2 distinct phases to ensure a thorough evaluation and implementation of this monitoring system (Table 1).

During phase 1 (the initial phase; months 1-3), patients will continue to receive the current standard of care, which involves manual spot checks and MEWS measurements by nursing staff. Concurrently, all health care staff will receive training on the application, data interpretation, and protocol adherence concerning the solution to optimize the infrastructure before its implementation.

Following phase 1 (in month 4; the evaluation and validation period), the preimplementation phase will be evaluated. Predictive accuracy will be evaluated by comparing device data against clinical outcomes such as complications, intensive care unit transfers, or MEWS-triggered interventions using area under the receiver operating characteristic curve analysis.

In phase 2 (months 5-8), the wearable will become the primary tool for patient monitoring, supplemented by manual spot checks by nurses as needed. This phase aims to evaluate the integration into standard care.

During the whole study, every minute data are securely stored. During phase 2 of the study, 6 times a day, median values of the previous 4-hour window will be uploaded to the EHR. In case of signal loss or low-quality readings, the system generates flags, allowing for assessment of signal-to-noise ratio (SNR).

**Table 1 table1:** Psychometric properties and statistical analysis.

Objective	Instrument	Variable	Statistical test	Achievement criteria
Fidelity	SUS^a^	Continuous	Unpaired *t* test or Mann-Whitney *U* test	Fidelity achieved when protocol adherence is ≥95%
Acceptance	SC^b^/day	Continuous	Descriptive statistics	Acceptance achieved when ≥75% of nurses use the device regularly
Acceptance	SC/patient	Continuous	Descriptive statistics	Acceptance achieved when ≥75% of nurses use the device regularly
Acceptance	IWS^c^	Ordinal	1-way ANOVA	Acceptance achieved when ≥75% of nurses use the device regularly
Adoption	EBPAS^d^	Continuous	Repeated measures ANOVA	Adoption achieved when device use exceeds 70% by clinical staff
Appropriateness	SNR^e^	Continuous	Descriptive statistics	Adoption achieved when device use exceeds 70% by clinical staff
Appropriateness	ADE^f^	Continuous	Descriptive statistics	Appropriateness achieved with minimal ADEs
Feasibility	Thematic analysis	Nominal	Braun and Clarke [11] thematic analysis	Feasibility achieved when 80% of clinicians can successfully implement the device
Time efficiency	Time measurement	Continuous	Descriptive statistics	Time efficiency achieved when nurses’ time spent on monitoring decreases by ≥20%
Predictive accuracy	MEWS^g^ and CREWS^h^	Nominal	AUROC^i^	Predictive accuracy achieved when AUROC ≥0.80

^a^SUS: System Usability Scale.

^b^SC: spot check.

^c^IWS: Integrated Workload Scale.

^d^EBPAS: Evidence Based Practice Attitude Scale.

^e^SNR: signal-to-noise ratio.

^f^ADE: adverse device event.

^g^MEWS: Modified Early Warning Score.

^h^CREWS: Continuous Remote Early Warning Score.

^i^AUROC: area under the receiver operating characteristic curve.

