### Outcomes

The primary objective of this study is to evaluate the implementation of a new wearable on the surgical ward at Catharina Hospital Eindhoven. This will be achieved by assessing its usability, degree of implementation, and the workload for nursing staff. The primary outcome will be acceptability, specifically evaluating workload as measured by the Integrated Workload Scale (IWS). The IWS is a comprehensive tool that provides multidimensional descriptions and gradations of workload, ranging from “not demanding” to “work too demanding” on a 9-point Likert scale. This scale is suitable for both periodic assessment and real-time monitoring of tasks, with measurements conducted throughout the entire study period.

For secondary outcomes, the study will apply the framework of the taxonomy of implementation outcomes of Proctor et al [12], focusing on adoption, feasibility, appropriateness, predictive accuracy, and technical feasibility. Adoption will be measured by the Evidence-Based Practice Attitude Scale and the System Usability Scale, along with the amount of spot checks conducted in addition to the standard monitoring.

Feasibility will be evaluated by determining the extent to which health care employees can successfully implement the device, and by measuring the time required to perform and process manual spot checks or digital monitoring checks. Appropriateness will be assessed by examining the SNR and counting the number of (suspected) adverse events that occur during or result from the use of the wearable.

Additionally, the predictive accuracy for early detection of health deterioration and postoperative complications among patients will be evaluated through focus group discussions. Technical feasibility will involve analyzing the availability of data on the web platform, including monitoring time and the types and quantities of algorithm artifacts, such as low-quality data during the monitoring of photoplethysmography values.

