## Discussion

This study is expected to demonstrate that the implementation of continuous vital sign monitoring using the viQtor wearable device is feasible within a surgical ward setting. We anticipate that this technology will be perceived as acceptable and usable by health care professionals, and that its integration may contribute to a measurable reduction in perceived nursing workload. Importantly, by including continuous SpO₂ monitoring, the system may offer added clinical value in identifying early signs of postoperative deterioration.

While earlier studies have assessed the technical accuracy of wearable monitoring devices, relatively few have focused on their integration into clinical workflows. For instance, Breteler et al [8] validated a similar system in high-risk surgical patients, but implementation outcomes such as usability or staff adoption were not the focus. Bellomo et al [7] also examined automated advisory systems, but their routine use in general hospital wards remains uncommon.

Our study distinguishes itself by applying a structured implementation framework, specifically the revised Medical Research Council guidance [10] and the taxonomy of implementation outcomes of Proctor et al [12]. This approach allows us to assess whether the device not only works but also can be realistically adopted in daily practice.

A notable addition in our protocol is the continuous monitoring of SpO₂, a parameter that was lacking in earlier studies such as those involving a Healthdot device. Since respiratory complications are among the more frequent and severe postoperative issues, continuous SpO₂ tracking may enhance the early recognition of patient decline [4,6,13].

The study’s multidisciplinary design, combining clinical, technical, and implementation expertise could be seen as a strength. The use of validated instruments—including the IWS [14], Evidence-Based Practice Attitude Scale [12], and the System Usability Scale—ensures a structured and multidimensional evaluation.

Limitations of this study can be expected as well. As a single-center trial focusing on patients undergoing elective surgery, its findings may not be directly generalizable to other hospital departments or to emergency or critical care populations. Additionally, while the viQtor device captures data at regular intervals, data loss or reduced signal quality could occur. These technical aspects will be explored through SNR analysis and artifact tracking.

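### The primary workload comparison is an uncontrolled before-after comparison on one ward, the test named for it adjusts for nothing, and the limitations do not say so

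*Protocol article*

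**What the plan says.** The abstract describes the study in these words: "is a prospective observational implementation study conducted over 8 months in a surgical ward". On workload it states: "We will also assess the impact on nursing workload and the usability of this workflow". The Outcomes section makes workload primary: "The primary outcome will be acceptability, specifically evaluating workload as measured by the Integrated Workload Scale (IWS"), a 9-point scale. About 70 nurses complete it.

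The roll-out has a fixed order. The Implementation Phase section says: "Implementation of the device as the new standard of care for monitoring will be executed in 2 distinct phases". First: "During phase 1 (the initial phase; months 1-3), patients will continue to receive the current standard of care". In the same months: "Concurrently, all health care staff will receive training on the application, data interpretation, and protocol adherence concerning the solution". Then: "In phase 2 (months 5-8), the wearable will become the primary tool for patient monitoring".

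Table 2 schedules the IWS at months 0 and 3, and then at months 5, 6, 7 and 8. Table 1 lists the IWS as ordinal and names a 1-way ANOVA for it, while the EBPAS gets a repeated measures ANOVA. The Statistical Analysis section gives a general rule that repeated measures are analysed by a linear mixed model or repeated measures ANOVA, and names no covariates.

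The Discussion anticipates that "its integration may contribute to a measurable reduction in perceived nursing workload". Its limitations cover generalizability from a single centre with elective patients, and possible loss of data or signal quality. They do not mention that the two phases lie in different calendar periods.

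**The concern.** The IWS measures how demanding the work feels. Patients per nurse, shift type and the time of year can plausibly move it with no device involved. All ratings before the device becomes primary come from earlier months than all ratings after it, on the same ward, with no ward that keeps the old workflow alongside. The before period also has only two occasions, and staff training runs during it.

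The test named in Table 1 compares occasion means and nothing else. A change in ward pressure between the phases would look the same as a device effect, in either direction, on the primary outcome. The abstract and Discussion speak of impact and reduction, so a reader may take a significant difference as evidence about the device.

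**Working it through.** The article gives no SD, effect size, alpha or sample-size calculation for the IWS, so there is no figure of its own to reproduce. Two checks follow.

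**1. What can be separated from phase**

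Input: the six IWS occasions in Table 2, months 0, 3 | 5, 6, 7, 8, with phase coded 0, 0 | 1, 1, 1, 1.

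- *Free month effects plus phase.* There are 7 columns (intercept, 5 month indicators, phase) of rank 6. No month falls in both phases, so phase is not estimable.
- *Linear trend plus phase.* The mean month is 29/6 = 4.83. The sum of squares of month is 183 − 29²/6 = 42.83, that of phase is 4/3, and the cross-product is 26 − 4 × 4.83 = 6.67. Hence r = 6.67/√(42.83 × 1.333) = 0.88, and the variance inflation factor is 1/(1 − 0.882²) = 4.5. The model is estimable, but weakly.
- *Annual sine and cosine plus phase.* Rank 4 of 4, with R² of phase on the seasonal terms 0.935 and a variance inflation factor of 15.4. It is estimable in name only.
- *Staffing, shift type, occupancy.* These are not functions of phase and can vary within each phase. They are possible confounders that can be adjusted for if recorded with the ratings.

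**2. How often the named test rejects when the device does nothing**

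Assumed, not in the documents: two-sided alpha 0.05, IWS SD 1.5 to 2.0, 70 ratings at each of the six occasions, independent ratings, and a ward-wide shift d in months 5-8 only.

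The noncentrality of the one-way ANOVA is λ = n × d² × Σ(phase − mean phase)²/SD². The sum is 2 × (2/3)² + 4 × (1/3)² = 4/3. The degrees of freedom are 5 and 414, and the critical F is 2.236.

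For d = 0.5:
- SD 1.5: λ = 70 × 0.25 × 1.333/2.25 = 10.37, rejection 69%.
- SD 2.0: λ = 70 × 0.25 × 1.333/4 = 5.83, rejection 42%.

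| Shift (points) | SD 1.5 | SD 2.0 |
|---|---|---|
| 0.25 | 19% | 12% |
| 0.5 | 69% | 42% |
| 1.0 | 100% | 98% |

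With 35 respondents per occasion and d = 0.5, the rates are 37% (SD 1.5) and 21% (SD 2.0). A direct phase contrast (140 against 280 ratings) with d = 0.5 rejects in 90% and 68%.

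*Effect of repeated ratings.* With a within-nurse correlation of 0.5, the error variance of the occasion differences halves, but the ANOVA denominator still carries the full variance. The test then rejects when a noncentral chi-square on 5 df with noncentrality λ/0.5 exceeds about 5 × 2.236/0.5 = 22.4. For d = 0.5 this gives about 60% (λ/0.5 = 20.7, SD 1.5) and 22% (11.7, SD 2.0), confirmed by simulation. With no shift at all it rejects in practically 0% of studies, so the named test is conservative in that case.

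*Random month-to-month shifts.* With ward-level shifts of SD 0.3 at each occasion, 70 respondents and SD 1.5, simulation gives 71% rejections with independent ratings and 64% with within-nurse correlation 0.5.

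**The case against.** **A reader might infer that season, occupancy and staffing are all inseparable from the device.** The documents do not support that. Only calendar time taken freely is exactly aliased. Occupancy and staffing vary within phases, so they are uncontrolled rather than inseparable.

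**A reader might infer that no stated analysis could adjust.** The Statistical Analysis section already allows a linear mixed model for repeated measures, and six scheduled IWS occasions fit that rule. A covariate list may stand in an analysis plan that is not shown, so the lack of one is not in itself the point. What stands is that Table 1 names a specific and different test for the primary outcome.

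**A reader might infer that any workload change will be reported as a device effect.** The study is labelled observational, the Discussion only says the device may contribute, and the criterion in the IWS row of Table 1 concerns regular device use by nurses, not a workload difference. That limits the consequence. The abstract does speak of impact, however, and no limitation tempers it.

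**The phase contrast is implied, not stated.** This is correct: it follows from the phases and the timetable. A 1-way ANOVA may equally be meant across all six occasions, which is how the main figures above were computed. Either way, months before and after the switch are compared.

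**Treating repeated ratings as independent might be thought to inflate false positives.** With the same nurses on each occasion it does the opposite; the cost is lost power for a real change.

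**Adjustment can itself mislead.** The abstract expects earlier discharge with wearables, so occupancy could lie on the path from device to workload. This stands, and it shapes the remedy.

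**Conclusion.** The concern holds in limited form. The primary workload comparison is before-after on one ward without a concurrent control, and calendar time is aliased with phase. Staffing and shift mix are left uncontrolled by the test that Table 1 names, and that entry sits uneasily with the article's own rule for repeated measures. The limitations are silent on this, and no analysis plan can remove the design feature.

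With no device effect, a ward-wide shift of 0.5 IWS point would be significant in about 69% to 42% of studies (assumed SD 1.5 to 2.0, 70 independent ratings per occasion), or about 60% to 22% if ratings within a nurse correlate at 0.5. Nothing in the documents shows that a 0.5-point shift is likely; the figures show sensitivity, not an expected error rate. The point deserves action as a cheap improvement and is not an objection to the design.

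**What to change.** 1. In Table 1, replace the 1-way ANOVA for the IWS with a linear mixed model, which the Statistical Analysis section already permits. Include phase, a random nurse intercept and, where a rating can be linked to a shift, shift type and patients per nurse from existing rosters.
2. Report adjusted and unadjusted phase effects side by side. Use ward occupancy only in a sensitivity analysis, because the device may affect length of stay. If ratings can be placed only by month, say so: a ward-level covariate then has about six values and adjusts little.
3. Add to the limitations that the design is before-after without a concurrent control and that season cannot be separated from phase. The model in step 1 does not solve this.
4. Word the conclusion as change in workload over the implementation period, not as a reduction due to the device.

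The cost is modest extraction of roster and bed data, a somewhat longer model and a weaker claim. No control ward, extra participants or change to care is needed.
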